## Abstract

**Background:**

At least 40% of people with psychosis have persistent distressing symptoms despite optimal medication treatment. Cognitive behaviour therapy for psychosis (CBTp) is the only NICE-recommended individual therapy for psychosis, with effects on symptoms, distress and quality of life. Yet <10% of service-users receive it and 94% of trusts struggle to provide it. Of those offered it, 22–43% refuse or do not attend. We have developed a new pre-CBTp informed choice intervention to address knowledge and attitudes that influence uptake and implementation and now want to test it in a feasibility trial.

**Methods:**

The design is a two-arm, feasibility randomised controlled trial (RCT), with 1:1 randomisation, stratified by participant group and site. Participants are 40 psychosis patients and 40 clinicians, who are ambivalent towards uptake or implementation of CBTp. Sites are community and inpatient services in Sussex and London. The intervention is a pre-CBT digital psychoeducation intervention designed to address identified knowledge and attitudinal barriers to uptake and implementation of CBTp, incorporating behaviour change mechanisms, and supported by animated introductory, patient and clinician stories. The comparator is the NHS choices website for CBT. The primary aim is to assess clinical feasibility (recruitment, randomisation, acceptability, use, delivery, outcome measurement, retention). A secondary aim is a preliminary evaluation of efficacy. Outcomes will be assessed at baseline, post intervention, and one-month follow-up (blind to treatment arm). The primary efficacy outcome is likelihood of offering/taking up CBTp. Secondary outcomes include knowledge and attitudes towards CBTp, illness perceptions, empowerment, psychological wellbeing (patients only) and CBTp implementation (clinicians only). Use of the intervention and CBT behaviours during the follow-up period will be recorded and captured in a feedback questionnaire. Use, acceptability and experience of outcome assessment will be explored in qualitative interviews with participants (*n* = 6 per group). The efficacy evaluation will report descriptive data, key model parameters and 95% highest probability density intervals in a Bayesian growth model.

**Discussion:**

This is the first feasibility trial of a digital ‘informed choice’ decision aid for the implementation of CBTp. If the trial proves feasible and demonstrates preliminary evidence of efficacy, a large multi-site trial will be warranted.

**Trial registration:**

ISRCTN registry, ISRCTN53107879. Registered prospectively on 2 August 2017.

**Electronic supplementary material:**

The online version of this article (10.1186/s13063-018-3023-7) contains supplementary material, which is available to authorized users.

## Background

People who experience psychosis comprise approximately 1% of the UK population (approximately 600,000 people). At least 40% have persistent distressing symptoms, and poor recovery, despite optimal medication treatment. Apart from the significant distress to patients, they make use of considerable NHS inpatient and community resources. The cost has been estimated at £6.7 billion [1]. Cognitive behavioural therapy for psychosis (CBTp) is the only NICE-recommended individual therapy for psychosis that is cost-effective [2–4] with effects in reducing hospitalisation, symptoms and distress, improving quality of life and social functioning [5–9]. Yet < 10% of service-users receive it and 94% of trusts struggle to provide it [10, 11] with similar problems and levels of implementation occurring internationally [12]. Moreover, of those offered it, 22–43% refuse or do not attend [13]^.^ There is a dearth of research into barriers to implementation in CBTp [14] and research on uptake is also limited.

In terms of CBTp delivery, diffusion, dissemination and implementation are progressively more active steps in translating the evidence into practice [15]. Dissemination is the process of distributing information to stakeholders, for example via guidelines, manuals and training, but it is insufficient to produce sustainable changes in practitioner behaviour [16]. Implementation of evidence-based health care presents a serious challenge and training transfer into routine practice is notoriously problematic [17]. A number of strategies are indicated to enhance implementation but no simple solution has been identified [18, 19].

These implementation strategies incorporate six key processes of planning, educating, financing, restructuring, quality control and policy content [19]. In relation to CBTp, identified barriers to implementation are consistent with these processes and include issues with workforce planning, shortages of trained staff and supervisors, limits in funding and in organisational support. However, at an individual level, limited knowledge and perceived relevance of psychological therapies, such as CBTp, and pessimistic attitudes on the part of clinicians also play a part [20, 21]. Specifically, implementation requires some change in the ‘adopter’ needs, motivations, values, goals and skills towards CBTp, again emphasising clinician knowledge, beliefs and attitudes. These cognitive factors might include perceived relative advantage of CBTp compared with other approaches, compatibility with one’s own views, health and illness perceptions, complexity and ease of use of the intervention and observability, or seeing it as achievable, watching it in action and knowing that it works [18, 22, 23]. Indeed, the Theory of Planned Behaviour requires that implementation is desirable, associated with positive attitudes and perceived to be within behavioural control [24], while Normalisation Process Theory proposes that implementation requires coherence with clinical practice, cognitive participation and engagement with the processes of intervention delivery, collective action of individuals, teams and services to support delivery, and reflexive monitoring of the impact of intervention delivery processes [25]. The knowledge and attitudes of clinicians are thus argued to be key to implementation of psychological interventions in psychosis [26–28] with some arguing that these attitudinal barriers may be at least as important to address as therapeutic skill training [29].

Significant steps have been made in addressing barriers at the organisational, financial, training and competency level with the advent of Improving Access to Psychological Therapies in Severe Mental Illness (Psychosis) (IAPT-SMI) national pilot sites and agreed competencies for therapy delivery. Indeed, Jolley and colleagues reported a threefold increase in accepted referrals for NICE-recommended CBTp in a single year, when supported by strong organisational readiness, established referral pathways, referral monitoring and managerial support, ring-fenced funding for trained therapists, and embedding within specialist psychosis service where staff were knowledgeable about the difficulties faced in psychosis and about appropriate treatments and engagement approaches [30]. Newer brief, intensive interventions may also help to improve implementation, as they can be targeted and delivered in shorter time frames [31–33]. However, there is still much to be done to increase implementation. The London IAPT-SMI pilot delivered to only 300 patients, from an estimated pool of 3500 eligible participants, and brief intensive interventions are not yet embedded within routine practice.

Only two small-scale qualitative studies in the UK have investigated implementation at the individual clinician level in terms of knowledge and beliefs, finding that barriers exist in terms of beliefs about who is appropriate for CBTp, who will accept it, who will benefit and who should deliver it [20, 21]. This pattern is repeated internationally, with low priority given to CBTp by clinicians in a recent German study, influenced by lack of availability of general and specialist CBTp training and limited normalising illness beliefs [34]. Kimhy et al. also found considerable knowledge gaps concerning the evidence base for CBTp in the US, even in psychiatry and psychology training directors [35].

However, improved implementation is only half of the picture. Uptake of interventions in general [36–39], and of CBTp in particular, may be hampered by health, illness and treatment perceptions [40–42]. Illness perceptions in psychosis patients also impact on quality of life [36–38]. Specific interventions, based on changing illness perceptions, have been effective in promoting adherence to and outcomes from physical health interventions and have emphasised the need to tailor these interventions to health beliefs [43, 44]. Brief interventions that encourage more adaptive beliefs about illness and informed choice regarding psychological treatment in psychosis are clearly needed [13, 45, 46], both to encourage uptake and to improve outcomes.

Hence, problems exist both in implementation by clinicians and uptake by service-users, with significant potential impact on prolonging distress and disability. NICE have emphasised the need for research to consider knowledge and beliefs when developing and evaluating interventions aimed at behaviour change among individuals or populations [2]. Interventions drawing on implementation science and health perceptions may provide the mechanism, while information technologies may offer the means of delivery, being easy to implement in routine care. Interactive web-based interventions hold the potential to bridge the ‘quality chasm’ enabling the delivery of effective standardised interactive materials, in accessible, flexible, cost and time-efficient formats, blending a range of approaches, that can be flexible to the knowledge, beliefs and behaviours of individuals, incorporating motivational and behaviour change techniques, and being readily refined through use and feedback [47–53].

In summary, CBTp is an effective intervention for distressing symptoms of psychosis yet few service-users receive it. Despite the potential for increased capacity to deliver CBTp through training, this has not translated well into increased implementation or uptake. This is in part hampered by gaps in knowledge and pessimistic attitudes. There has been little research aimed at addressing these gaps.

### Research question

Is a randomised controlled trial (RCT) of a pre-CBTp digital ‘informed choice’ intervention to improve knowledge, beliefs and behaviours of clinicians and service-users feasible to be implemented?

### Aims and objectives

This is the first feasibility RCT to develop and test a pre-CBT digital ‘informed choice’ psychoeducation intervention, designed to address identified knowledge and attitudinal barriers to uptake by psychosis patients and offers by clinicians of CBTp, and ultimately to improve implementation. The primary research aim is to explore trial methods, clinician and patient acceptability of the interventions and outcome measures, and to provide data to estimate the parameters required to design a future RCT. The primary objectives are as follows:To determine the number of participants who accept referral and randomisation (benchmark set at 80% of target for progression);To evaluate the appropriateness of eligibility criteria (ambivalence towards CBTp) by determining feasible eligibility and recruitment rates at each site;To assess retention through post-intervention and one-month follow-up rates (benchmark set at minimum 80% retention in line with previous studies);To assess acceptability of the intervention, and factors influencing this, through usage data in the follow-up period, feedback questionnaire responses, and qualitative interviews;To assess the acceptability and feasibility of the outcome measures as methods to measure efficacy of the intervention within a future trial.

Secondary objectives will be:To measure and describe key outcomes post intervention and at one-month-follow up (e.g. completion rates, likelihood of offering/referring or taking CBT). Descriptive statistics will be used to quantify dropout and differences in mean responses on key outcome measures over time within each arm. Contingent upon the similarity of protocol for a future trial to this feasibility trial, Bayesian models may be fit to determine plausible estimates for the effect of the trial under both informative and uninformative priors.

We will not report significance tests as the feasibility RCT was not designed or powered to test hypotheses or to detect change. We have selected the NHS choices information about CBT as the comparison intervention as this is the next best alternative online resource about CBT that is routinely available for use by NHS clinicians and the public.

## Method

### Design

The design is a two-arm, multicentre, longitudinal, feasibility RCT, with 1:1 block randomisation and varying block size, stratified by participant group (clinician or patient) and site (London or Sussex). Participants will be randomised by Kings College London Clinical Trials Unit, independently from the trial team, using an online randomisation system. Randomisation will be initiated by the research assistant immediately after the baseline assessment and before intervention delivery. Allocation will be confirmed by email. Baseline and one-month follow-up data will be collected blind to allocation to ensure unbiased data collection. Post-intervention data will not be collected blind to allocation as these data are collected in a single session, immediately after intervention delivery. Participants will not be blind and will be reminded of the blind procedure at the start of the one-month follow-up, in order to reduce the risk that they reveal their allocation, and blind breaks will be recorded. For reporting the feasibility of the RCT, the CONSORT (Consolidated Standards of Reporting Trials; http://www.consort-statement.org/) extension to randomised pilot and feasibility trials statement will be followed [54]. For the protocol, the SPIRIT (Standard Protocol Items: Recommendations for Interventional Trials) Figure and Checklist are provided in this paper see: Fig. 1 and Additional file 1.

**Fig. 1 Fig1:**
[figure not shown]
Figure for Standard Protocol Items (SPIRIT) for an interventional trial of a pre-CBT digital ‘informed choice’ psychoeducation intervention for clinicians who work with psychosis and their psychosis service users (the U&I study): schedule of enrolment, interventions, and assessments

### Setting

The setting will be secondary NHS community and inpatient services in two geographically distinct NHS Trusts: Sussex Partnership NHS Foundation Trust (rural and urban) and South London and Maudsley NHS Foundation Trust (urban inner city).

### Participants

Participants will be 40 current psychosis patients and 40 clinicians working with people with psychosis, aged 16–65 years, who have expressed ambivalence towards uptake or implementation of CBTp.

Inclusion criteria are:A current psychotic disorder diagnosis (F20-F29 ICD-10 diagnoses) as evidenced by clinical notes and/or discussion with lead mental health professional (patients only);Receiving treatment from secondary mental health services for psychosis or working as a clinician in a secondary mental health service that delivers treatments for psychosis;Age 16–65 years;Holding ambivalent views regarding CBTp, (defined as a score of ≤ 7 on a 10-point Likert scale for likelihood of taking up CBTp (patients) or offering/referring for CBTp (clinicians).

Exclusion criteria:Lack of capacity to give informed consent;Insufficient grasp of the English language to enable questionnaire completion;Cognitive impairment or learning disability which precludes engagement with the study materials.

### Trial flowchart

Figure 2 illustrates the trial flowchart.

**Fig. 2 Fig2:**
[figure not shown]
Trial flowchart for the U&I study feasibility RCT protocol

### Intervention development

The intervention was developed over three phases of user-centred design and research process. The purpose of these phases was: (1) to identify a rich set of issues affecting uptake and implementation through a qualitative study; (2) to identify the largest and most significant of these issues in two large quantitative questionnaire studies; and (3) to develop a broad set of intervention components and to select the most important of these through workshops and a Delphi consultation.

First, qualitative interviews were conducted with 37 clinicians and 27 patients with psychosis in order to determine the nature of knowledge and attitudinal barriers to uptake and implementation of CBTp. The interviews were transcribed and analysed thematically; the content was used to develop the two knowledge and attitudes towards CBTp questionnaires (described below). In phase 2, these questionnaires were given to 206 clinicians and 206 patients; the data were used to identify the most significant factors influencing uptake and implementation. In phase 3, a user-centred design approach, and workshops with patients, clinicians and the research team, led by an industrial designer and Uscreates, a health design agency, developed and tested the design concepts, components and functions. The initial stories and content were informed by the rich qualitative data, questionnaire data and workshops. A Delphi consultation with clinicians, patients, CBT trainers and experts in digital therapy (*n* = 12) reached consensus on components of the final intervention.

### Intervention

The pre-CBT digital ‘informed-choice’ psychoeducation intervention is a website with information, animated stories and interactive elements, designed to address identified knowledge and attitudinal barriers to uptake and implementation of CBTp in clinicians and patients. It provides honest, balanced and hopeful information, incorporating behaviour change mechanisms derived from the theory of planned behaviour, and models of health perceptions, and is supported by animated introductory, patient and clinician stories. An interactive goals section aims to encourage motivation, while the stories, allow patients and clinicians to compare themselves to others with similar experiences, and to see CBTp in action, and hear how it works. The intervention includes sections on what CBTp is; how and whether it works; what it can help with and for whom; how it compares to alternative treatments; what CBTp might be like, and advice on preparing to start CBTp. It also contains handouts and sections for family and friends, and for the whole clinical team, which aim to promote a cohesive and supportive social and clinical network for the implementation of CBTp. The animated stories are an especially important component. They incorporate key messages derived from the earlier stages of intervention development. They can be watched either as complete stories or in sections that illustrate the three main topics: What is CBTp? What will it be like? And Is CBTp for me?

The order of accessing the materials is fixed and participants are encouraged to visit the different sections in order, following a journey represented by a sailing boat, through the intervention, with a route map and arrows that indicate the direction of travel. Although the participant can select their own ‘goals’ within the intervention and print these, no data are saved, thus avoiding patients’ concerns about personal data security. Although the intervention is designed for both patients and clinicians, patients felt strongly that they should have access to the same information as clinicians, while clinicians felt that the intervention should be geared towards the needs of patients; as such, only a single intervention platform was developed.

The intervention will be delivered during a manualised introductory session of up to 1-h duration, by a trained research assistant. Access to the intervention will be available for the subsequent month by computer or iPad, before follow-up. No specific instructions will be given for how or when participants should access the intervention, but overall usage data will be recorded. Images of the intervention are shown in Fig. 3.

**Fig. 3 Fig3:**
[figure not shown]
The intervention website. **a** The home page. **b** A patient’s story. **c** An interactive page

The manual comprises a three-page document, which describes how to introduce the digital intervention to a clinician or a service user. The introduction explains: (1) how the intervention has been developed; (2) the prominent features of the intervention that are of relevance for each type of user (clinician or service user); and (3) the way in which each type of user might use the intervention in the subsequent month. Subsequent sections of the manual describe which sections of the intervention to visit, in which order, for how long, and which features and functions should be demonstrated and content emphasised in each section. Finally, the manual directs the research assistant to provide the user with an information sheet with the website address and space to record their experiences of use in the subsequent month.

Each research assistant who delivers the intervention will be provided with the manual and the intervention and will be required to practice delivery with and ask questions of a trained colleague to ensure confidence and competence before first use.

### Comparator

The active comparator intervention is the CBT section of the NHS choices website. It controls for attention and intention and represents best-case routine care in relation to CBT decision-making. It contains written text in five sections: How CBT works; Uses for CBT; What happens during a session; Pros and Cons of CBT; and Finding a therapist. It also includes a short, written user story. It will be presented in an equivalent session of up to 1 h, with a printed summary sheet provided as a handout, alongside the link to the website for use in the subsequent month.

All routine care and interventions will be permitted throughout the duration of the study.

### Assessments of outcome

Please refer to Fig. 1 (SPIRIT figure) for details of assessment at each visit. The sample sizes have been determined by pragmatic means to establish the feasibility of study and intervention procedures.

### Primary feasibility outcomes

The primary purpose is to assess the feasibility of the interventions in terms of acceptability, usability and accessibility, and to examine the feasibility of methods of a future trial including measures, recruitment procedures and trial processes. This will be done through monitoring using the study CONSORT diagram, through system analytics on use of the digital intervention during the one-month period, through the user feedback questionnaire collected at the end of one month, and through a qualitative interview with a sub-sample of those receiving the intervention (*n* = 6 per group) at the end of one month. The primary feasibility outcomes are:Feasibility of eligibility criteria, recruitment and retention within the NHS (numbers referred, recruited, consented, randomised and retained in the trial) during the trial recruitment period of August 2017 to May 2018;Feasibility of use, accessibility and acceptability of the intervention and the outcome measures in the NHS, measured using feedback questionnaire responses regarding use of the intervention; activity data on use of the intervention during the follow-up period (average number of pages visited per participant), qualitative interviews with six patients and six clinicians (three each in Sussex and London) regarding their experience of using the intervention, the selection of outcome measures and participation in the trial; September 2017 to May 2018.

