### Data management and security

Data storage and confidentiality will be ensured, in line with the Data Protection Act 1998 and the NHS Code of Practice for Confidentiality. All personally identifiable data will be kept separately from anonymised research data and all data will be stored in secure password-protected files, available only to the study team, on Sussex Partnership NHS Foundation Trust protected access shared drives and in locked filing cabinets. Study data will be identified using a participant identification number (ID). This ID will be linked to the participant’s name in a password protected link file. Audio-recording equipment will be used to record qualitative interviews regarding the experiences of taking part in the intervention and the trial. These audio files, named with the unique participant identifier, will be stored as computer files on secure NHS servers in an anonymised and encrypted form.

The digital intervention will record how patients and clinicians use the intervention over the month that they have access, including which pages are accessed and how frequently. Only data about use of the package will be stored. No personal data will be stored. Usage data will be tracked through Google Analytics and stored safely and confidentially in an encoded and password-protected format that prevents tampering and that is only accessible to the researchers.

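### The only objective measure of intervention use is fixed as a mean page count, which cannot show how many participants returned to the site

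*Protocol article*

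**What the plan says.** Under Primary feasibility outcomes, the protocol article lists three sources on use and acceptability: feedback questionnaire responses, site analytics, and qualitative interviews with six patients and six clinicians. For the analytics it names one summary: "activity data on use of the intervention during the follow-up period (average number of pages visited per participant". The fourth primary objective (Aims and objectives) is to assess acceptability, and what influences it, partly through these usage data.

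On the data source, Data management and security states: "Usage data will be tracked through Google Analytics and stored safely and confidentially in an encoded and password-protected format". It adds: "Only data about use of the package will be stored. No personal data will be stored". It also says that "The digital intervention will record how patients and clinicians use the intervention over the month that they have access, including which pages are accessed"; the frequency of access is recorded too. The Intervention section says that participants get no specific instructions on how or when to use the site, "but overall usage data will be recorded". Patients and clinicians share the site, since "only a single intervention platform was developed". The research assistant gives each user the web address on an information sheet.

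Use is also asked about directly. Under Procedure, everyone in the intervention arm completes a feedback questionnaire on their use. Under Efficacy evaluation outcomes, a follow-up interview of about 10 minutes covers use as well.

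**The concern.** The feasibility question is whether people come back to the site after one guided session of up to an hour. That is first a question about a proportion of people, and only then about how much they viewed. Where use is optional, some participants may view nothing and a few may view a great deal. A mean merges the two questions, so broad light use and heavy use by one or two people can give the same figure.

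A second matter follows from the first. A per-participant figure of any kind, and a figure for each group, needs visits to be tied to a participant or at least to a group. The article mentions no log-in, study code or group-specific link.

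At stake is what the future trial can learn about engagement. The Analysis plan uses the feasibility work to refine the intervention. The Discussion says that the team must understand how far one site meets clinicians' needs alongside those of patients. A mean page count helps little with either.

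**Working it through.** **Plan's own figure.** There is none to reproduce. The sample size is pragmatic (Assessments of outcome), and no target for use is stated.

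**Inputs from the article.** 40 patients and 40 clinicians (Participants); 1:1 randomisation stratified by group and site (Design). Expected number in the intervention arm: 40 × 1/2 = 20 per group, 80 × 1/2 = 40 in all. Blocking makes these approximate.

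**Inputs assumed.** The article gives no page counts. The patterns below are illustrations of what a mean can hide, not forecasts.

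**Step 1: one group of 20.** Mean = total pages / 20.

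| Pattern | Mean pages | Any use | Median |
|---|---|---|---|
| All 20 view 10 | 200/20 = 10 | 20/20 = 100% | 10 |
| 2 view 100, 18 view none | 200/20 = 10 | 2/20 = 10% | 0 |
| 1 views 200, 19 view none | 200/20 = 10 | 1/20 = 5% | 0 |

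The third row also shows the leverage of one person: 200 pages move the group mean by 200/20 = 10.

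**Step 2: if the two groups were reported together (n = 40).** The article does not say that they will be; this shows why the split matters.

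| Pattern | Mean pages | Any use | Clinician mean | Patient mean |
|---|---|---|---|---|
| All 40 view 10 | 400/40 = 10 | 100% | 10 | 10 |
| 10 clinicians view 40, the other 30 people view none | 400/40 = 10 | 25% | 20 | 0 |
| 20 clinicians view 20, patients view none | 400/40 = 10 | 50% | 20 | 0 |
| Clinicians view 5, patients 15 | (100 + 300)/40 = 10 | 100% | 5 | 15 |

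One combined mean of 10 fits 25% to 100% users, and patient means from 0 to 15.

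**Step 3: what the proportion would deliver at n = 20.** Wilson 95% interval: centre (p + z²/2n)/(1 + z²/n), half-width z√[p(1 − p)/n + z²/4n²]/(1 + z²/n), with z = 1.96.

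- 2/20: centre (0.100 + 0.096)/1.192 = 0.164; half-width 1.96 × √(0.0045 + 0.0024)/1.192 = 0.137; so 10% (3% to 30%).
- 20/20: centre (1 + 0.096)/1.192 = 0.919; half-width 1.96 × √0.0024/1.192 = 0.081; so 100% (84% to 100%).
- By the same formula, 5/20 gives 25% (11% to 47%), 10/20 gives 50% (30% to 70%) and 15/20 gives 75% (53% to 89%).

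The intervals are wide. Even so, the first two patterns in Step 1, which the mean cannot tell apart, have intervals that do not overlap.

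**The case against.** The strongest reply is that the mean page count does not stand alone. The same outcome also rests on a feedback questionnaire from everyone in the intervention arm, and the follow-up interview asks about use. Both belong to a known person in a known group. This stands, and it limits the point: who used the site, and in which group, can be reported by self-report. The analytics remain the only objective source. The questionnaire also reaches only those still in the study at one month. At the article's own 80% retention benchmark, 20% of 20, or 4 people per group, could be missing from it.

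A reader might infer that the analytics can never identify users or separate patients from clinicians. The documents do not support that. Storing no personal data does not exclude a pseudonymous code. The article says that use by patients and by clinicians will be recorded, and its own summary is per participant. The reference to overall usage data points the other way, so the text is unclear rather than contradictory. Nor does it say that the groups will be pooled.

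A reader might also infer that other people's visits inflate the counts, because "It also contains handouts and sections for family and friends, and for the whole clinical team". The article does not say that these people visit during the trial or that their visits are counted, so this is only a possibility.

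Finally, medians, intervals and tables by group are often left to an analysis plan, and their absence alone would be no finding. Here the article has fixed a summary for part of a primary feasibility outcome, and that choice can be judged.

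**Conclusion.** The point holds as a criticism of the chosen summary. A mean page count cannot show how many participants returned: at about 20 per group, a mean of 10 fits anything from 5% to 100% users in the patterns shown. This arithmetic needs only the group size. How far it matters in practice depends on how uneven use turns out to be, which the article gives no basis to predict. The limitation remains even if every visit is linked to a participant.

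The missing account of how visits are attributed is secondary. It calls for a clear statement and does not show that attribution is impossible.

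The consequences are limited. The numerical benchmarks under Aims and objectives concern recruitment and retention, both at 80%. No progression rule, sample size or efficacy estimate depends on mean pages. What is affected is the value of the objective usage data for judging acceptability and planning the next trial.

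**What to change.** Replace the mean as the lead summary of the analytics. For patients and clinicians separately, report:

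- the percentage with at least one visit after the introductory session, with a 95% interval and everyone allocated to the intervention as the denominator;
- the median and IQR of visits and of pages;
- the mean as a supplement.

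Exclude visits by research staff and pages opened during the introductory session. Changing the summary costs almost nothing.

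State how visits are attributed. A coded link or log-in carrying only the study ID would serve. The cost is small: setting it up, and telling participants that coded use is logged. It has to be in place before use is logged and cannot be added for months already elapsed.

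Where coding is not possible, say that the analytics are aggregate only, and take the proportion using the site, by group, from the feedback questionnaire, labelled as self-report.
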